### Sample size considerations

The sample size determination was undertaken considering the cluster randomized study design [21]. An estimated sample size of 738 mother-child pairs will be required for both intervention and control arms so as to have adequate power to detect an increase in exclusive breastfeeding for 6 months from 32 % (the baseline rate of exclusive breastfeeding in the study setting) [17] to 50 %; an approximately 18-percentage point increase, although higher increases have been documented in similar interventions elsewhere in the developing world [22]. We used a level of precision of 5 % (for a 2-sided *t* test) and power of 80 %. We then adjusted for expected design effect using a design effect of 3.15 calculated based on intracluster correlation coefficient of 0.035 from another study in Kenya (unpublished) and an average cluster size of 62.5. We allowed for 10 % potential loss to follow-up. The estimated sample size is 812. We therefore expect to recruit 406 women in each study arm. Twelve CUs will be required for the estimated sample size.

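### The stated 80% power rests on a normal approximation; with six unmatched community units per arm (10 degrees of freedom) it is about 72–73%

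*Protocol article*

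**What the plan says.** Under Sample size considerations, the protocol article takes a control rate of 32% and a target of 50%, "an approximately 18-percentage point increase". It uses a 5% level "for a 2-sided *t* test) and power of 80" per cent. It then inflates for clustering: "We then adjusted for expected design effect using a design effect of 3.15 calculated based on intracluster correlation coefficient of 0.035", with an average cluster size of 62.5. This gives 738 mother-child pairs over both arms. After an allowance of 10% for loss to follow-up, "The estimated sample size is 812", or 406 women per arm. The section ends: "Twelve CUs will be required for the estimated sample size".

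Study design and randomization says that thirteen CUs are defined and that twelve are randomised, half to each arm, without matching. Neither section mentions a correction for the small number of clusters.

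**The concern.** A design effect inflates the variance for correlation within clusters. It does not allow for the fact that the between-cluster variance is estimated from very few clusters. With six per arm, the between-arm comparison has 2 × (6 − 1) = 10 degrees of freedom, so a valid two-sided 5% test needs a critical value of 2.23 and not 1.96. If 738 was derived with 1.96, the stated 80% is not a property of this design, although the section itself names a t test.

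The trial is meant to inform national roll-out of the initiative. A non-significant result would be weighed against a claimed 20% chance of missing an 18-point effect, when that chance is nearer 27–28%.

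**Working it through.** **Inputs.** From Sample size considerations: p1 = 0.32, p2 = 0.50, difference 0.18, two-sided alpha 0.05, power 0.80, intracluster correlation (ICC) 0.035, cluster size 62.5, 738 before loss and 812 after. From Study design and randomization: six CUs per arm, unmatched.

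**1. Reproducing the plan's figures**
- Unpooled variance: 0.32 × 0.68 + 0.50 × 0.50 = 0.4676. Pooled variance: 2 × 0.41 × 0.59 = 0.4838.
- Individually randomised size per arm, pooled: (1.96 + 0.8416)² × 0.4838 / 0.18² = 117.2. The formula with pooled variance under the null and unpooled under the alternative gives 116.01, rounded up to 117.
- Design effect: 1 + (62.5 − 1) × 0.035 = 3.1525.
- Total: 2 × 117 × 3.15 = 737.1, or 2 × 117.2 × 3.15 = 738.4. The stated figure is 738.
- Loss: 738 × 1.1 = 811.8, stated as 812.

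The plan's figures therefore reproduce, and they do so with the normal critical value.

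**2. Power with 12 clusters at 738 analysed**
- Pairs per cluster: 738 / 12 = 61.5. Design effect at that size: 1 + 60.5 × 0.035 = 3.1175.
- Standard error, unpooled: sqrt(0.4676 × 3.1175 / 369) = 0.0629. Noncentrality: 0.18 / 0.0629 = 2.86.
- Standard error, pooled: sqrt(0.4838 × 3.1175 / 369) = 0.0639. Noncentrality: 2.82.

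| Test | Unpooled | Pooled |
|---|---|---|
| Critical value 1.96 (normal) | 81.7% | 80.4% |
| Critical value 2.23 (noncentral t, 10 df) | 73.3% | 71.9% |
| As above, all 812 analysed (67.7 per cluster) | 74.5% | 73.1% |

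A beta-binomial simulation of a two-sample t test on six versus six cluster proportions (40,000 runs, 61 to 63 pairs per cluster) gave 72.5–72.7%.

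**3. Effect detectable with 80% power, 10 df, 738 analysed:** 32% versus 51.5% (unpooled) or 52.0% (pooled).

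**4. Type I error if 1.96 is used with a 10-df statistic:** P(|t10| > 1.96) = 7.8%.

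**5. Sensitivity to the ICC.** The alternative values are assumptions (10 df, 61.5 per cluster).

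| ICC | Unpooled | Pooled |
|---|---|---|
| 0.02 | 86.5% | 85.3% |
| 0.035 (plan) | 73.3% | 71.9% |
| 0.05 | 62.3% | 60.9% |
| 0.07 | 51.5% | 50.1% |

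**6. More clusters or more women.** Seven clusters per arm at 61.5 pairs gives 81.0% (unpooled) or 79.7% (pooled), but that is 14 CUs and 13 are defined. Keeping 12 CUs, 80% needs about 121 (unpooled) to 148 (pooled) analysed pairs per cluster, or about 1,450 to 1,780 in total.

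**7. Loss allowance.** A 10% loss from 812 leaves 812 × 0.9 = 730.8, below 738; 738 / 0.9 = 820. The allowance actually made is (812 − 738) / 812 = 9.1%. At 730.8 analysed, power is 73.2% instead of 73.3% (unpooled), a difference of about 0.1 point.

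**The case against.** The strongest reply is that the 10-df test is partly inferred. The section names a t test but does not say that it is applied to twelve cluster proportions. Statistical analysis plans individual-level regression models that account for clustering, with covariates, and the degrees-of-freedom method may be set in an analysis plan that is not shown. This stands as a reason to state the 72–73% conditionally. It does not rescue the 80%: a method that corrects for few clusters has roughly the lower power, and one that does not correct reaches 80% only with a type I error above 5%.

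It is also fair that uncertainty in the ICC runs both ways. The value comes from an unpublished study, and at an assumed 0.02 the design exceeds 80% even with 10 df. The section notes that larger increases have been seen elsewhere, and the detectable effect lies only 1.5 to 2 points beyond the target. The study is also described as a pilot.

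A reader might infer more than the documents support:
- That the loss allowance causes the shortfall. It is 8 women and about 0.1 point of power.
- That a normal-theory test here has a type I error near 10%. For a 10-df statistic it is 7.8%; a higher figure needs an uncorrected variance estimator that the protocol does not name.
- That unequal CU sizes or pregnancy losses lower power further by a known amount, so that a recruitment quota per CU is required. The documents give no spread of cluster sizes and no loss rates from which to calculate this.

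**Conclusion.** The 80% is wrong as written. It belongs to a normal approximation that treats the twelve CUs as if they were many. For 32% versus 50% at 738 analysed, power is about 72–73%, a shortfall of 7 to 8 points; if all 812 contribute it is 73–74.5%. This rests on an ICC of 0.035, equal clusters, no covariate adjustment and a test that holds 5% type I error on 10 df. The statement that twelve CUs are what the sample size requires falls with the 80%.

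The point concerns a stated property of the design. It does not show that the trial is invalid or that the primary analysis must change.

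**What to change.** In Sample size considerations:
- State that, with twelve CUs and a test on 10 degrees of freedom, power is about 72–73% for 32% versus 50%, and 80% for about 32% versus 51.5–52%, and list the assumptions.
- Show power over an assumed ICC range in both directions: about 85–86% at 0.02, 61–62% at 0.05 and 50–51% at 0.07.
- Replace the sentence that twelve CUs are required with one saying that twelve are used and give this power.
- As a minor correction, describe the loss allowance as about 9% (738 retained out of 812).

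The cost is a few sentences and a less favourable stated power. No clusters or women need to be added.

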### Intervention

The intervention will involve implementation of the BFCI in the intervention clusters. The proposed BFCI in Kenya is a multifaceted program for promotion of optimal breastfeeding and infant and young child nutrition, and other practices including maternal nutrition in the community. The BFCI is based on the principles of the BFHI, but extends them to the community in order to provide women with a comprehensive support system to improve breastfeeding practices and other maternal, infant and young child nutrition practices at the community level. The BFCI package (unpublished) adapted for implementation in Kenya involves an 8-step plan as illustrated in Table 1.

**Table 1 Tab1:** Steps in the proposed Baby Friendly Community Initiative (BFCI) program in Kenya

Step	Description
Step 1	Have a written MIYCN policy summary statement that is routinely communicated to all health providers, community health volunteers and community
Step 2	Train all health care providers and community health volunteers in the knowledge and skills necessary to implement the MIYCN policy
Step 3	Promote optimal maternal nutrition among women and their families
Step 4	Inform all mothers and their families about the benefits of breastfeeding and risks of artificial feeding
Step 5	Support mothers to initiate breastfeeding within the first hour of birth, establish and maintain exclusive breastfeeding for first 6 months
Step 6	Encourage sustained breastfeeding beyond 6 months to 2 years or more alongside timely introduction of appropriate, adequate and safe complementary foods
Step 7	Provide a welcoming and conducive environment for breastfeeding families
Step 8	Promote collaboration between health care staff, maternal, infant and young child nutrition support groups and the local community

*MIYCN* maternal, infant and young child nutrition

CHWs (including traditional birth attendants (TBAs)) and health care professionals at the lower-level health facilities (dispensaries (level 2) and health centers (level 3)) in the participating intervention CUs will be trained on the BFCI package at the beginning of the intervention followed by on-job training and mentoring through supportive supervision by the research team and the sub-county Nutrition Officer quarterly to ensure proper implementation of the BFCI at the facility and community levels. Training materials for CHWs and health professionals will include the IYCF Counseling Package developed by UNICEF in partnership with other organizations, which has been adopted by the Ministry of Health, Kenya [23]. The package is designed to equip primary health care staff to be able to support mothers and other caregivers to optimally feed their infants and young children. The CHWs and primary care staff will be equipped with infant and young child feeding counseling cards; brightly colored illustrations that depict key infant and young child feeding concepts and behaviors to share with mothers, fathers and other caregivers. The package will be adapted to include counseling messages on maternal nutrition.

As part of the BFCI package, community support groups for mothers comprising about 20 mothers per group and including other people in the community that may support the mothers such as a CHW, a community health extension worker, an older woman and a community leader, will be formed in the intervention areas. The mothers in the group will meet regularly: for example, once a month to offer each other peer-counseling and support with regards to breastfeeding and other maternal, infant and young child nutrition practices. The CHW will be the facilitator of the group. The older woman will be a model mother, carefully selected, based on knowledge and experience with infant feeding, and will be a resource for the group. The community leader, who may be the area chief or village elder, will also be a resource person particularly to offer support on administrative issues. The extension worker, who may be a skilled nurse will offer technical advice to the group.

CHWs in both intervention and control areas will be given a motivation package given as a seed grant to the whole group of CHWs to start an income-generating activity, and training on income-generating activities.

The intervention group will also receive the BFCI package including: (i) personalized home-based counseling and support on optimal MIYCN practices by CHWs, and professional counseling of mothers by health professionals at health facilities; and (ii) formation of community support groups for mothers. In addition, they will receive MIYCN education materials. The control group will have the usual care only (Table 1). Usual care will include routine services offered to mothers and their children through the health care system including information materials regarding MIYCN, standard counseling on antenatal and postnatal care, appropriate tests during pregnancy, health facility delivery, general nutrition, hygiene, and immunization. Those in the control arm will receive routine visits by CHWs as provided for within the Community Health Strategy (usual care). Table 2 outlines the intervention package.

**Table 2 Tab2:** Services and materials provided to intervention and control groups

Intervention group	Control group
a) Distribution of MIYCN educational materials (usual care)	a) Distribution of MIYCN educational materials (usual care)
b) Supportive supervision (scheduled regular visits to assess implementation of BFCI package)	b) Supportive supervision (usual planned visits by DHMT)
c) CHW motivation package (provision of a monthly stipend (seed money for an income generating activity as a group) and training for income-generation activities as incentive)	c) CHW motivation package (Seed money for an income generating activity as a group same as in the intervention group)
d) Orientation, and continuous on job training and mentoring of the HWs and CHWs/CHEWs on BFCI package implementation	
e) Formation and support of mother support groups in the community	

*BFCI* Baby Friendly Community Initiative, *CHEWs* community health extension workers, *CHWs* community health workers, *DHMT* district health management team, *HWs* health workers, *MIYCN* maternal, infant and young child nutrition

Counseling of mothers will be initiated during pregnancy as soon as the mother is recruited and will be continued until the infant is 6 months. Counseling will encompass maternal nutrition, skin-to-skin contact between mother and baby immediately after birth, immediate initiation of breastfeeding after birth, breast positioning and attachment, exclusive breastfeeding, frequency and duration of breastfeeding, expressing breast milk, storage and handling of expressed milk and lactation management. It will also focus on age-appropriate complementary feeding, starting at 6 months: age appropriate complementary foods (nutritious, safe, affordable, and locally available), feeding frequency and quantity, and appropriate feeding practices including hygiene and responsive feeding behaviors, which encourage mother-child interaction during feeding [24, 25]. However, effectiveness of the intervention on complementary feeding will not be evaluated in this study. For the intervention arm, CHWs will visit the pregnant woman about once every month up to week 34, after which they will visit the mother weekly until delivery. After delivery, they will visit the mother weekly in the first month, then once a month until 6 months. The CHWs to be involved will be existing CHWs within the existing CUs in the region under the Community Strategy. In line with guidelines of the Community Health Strategy in Kenya, each CHW will serve approximately 20 households. HIV-infected women will not be excluded nor their status identified in the data collection. The counselors in the intervention arm will be trained on the messages for both HIV-negative and HIV-positive mother with regards to infant feeding. The information materials given to both intervention and control arms will also stipulate information on feeding for HIV-exposed infants. The CHWs will further be told to inform the mothers that should they be HIV-positive, they should seek further counseling and support from health professionals/PMTCT program. An outline of the content of the counseling messages is given in Table 3.

**Table 3 Tab3:** Content of counseling messages

• Maternal nutrition:	
	Food portions during pregnancy and lactation
	Appropriate foods (nutritious, affordable, and locally available) during pregnancy and lactation
	Frequency of feeding during pregnancy and lactation
• Breastfeeding:	
	Breast positioning and attachment
	Immediate initiation of breastfeeding after birth
	Exclusive breastfeeding for 6 months
	Frequency and duration of breastfeeding
	Expressing breast milk, storage and cup feeding
	Dealing with breast conditions
	Breastfeeding for HIV-positive women
• Complementary feeding:	
	Timely initiation of complementary foods
	Appropriate complementary foods (nutritious, affordable, and locally available)
	Feeding frequency and quantity
	Appropriate feeding practices including hygiene and responsive feeding behaviors
	Safe preparation and storage of foods

A formative qualitative study will be conducted before the roll-out of the intervention to inform the design and components of the intervention including content of the counseling messages. Interviews will be conducted with: (i) key informants in the study communities such as community leaders, CHWs, TBAs and health professionals; (ii) women who are currently pregnant, breastfeeding or mothers of children under 5 years. Additionally, consultations will be held with key organizations including the Division of Nutrition and Dietetics and the Division of Community Health Services in the Ministry of Health; UNICEF and other organizations working on MIYCN issues. The information gathered will be used to adapt the counseling messages and information materials. The formative study will also establish mechanisms for successfully engaging CHWs into the study.

Rigorous monitoring of the intervention will be done to ensure that the intervention is delivered as required. Process evaluation of the intervention will be done at mid-term and at end-line using the assessment tools specifically developed for the purpose. Exit interviews will be conducted with pregnant women and mothers of children aged less than 6 months at the health facilities in the intervention CUs on the counseling on MIYCN received. Another set of similar interviews will be conducted at the community level in the participating CUs. Additionally, interviews will be conducted with CHWs and health care professionals: for example, to establish if they actually obtained training on MIYCN. Further, observations will be done to determine whether BFCI is being implemented as planned: for example, if there is a written policy summary statement at the participating health facilities that is routinely communicated to health care workers. Process evaluation will lead to determination of whether the health facility should be certified as baby friendly or not as outlined in the BFCI assessment protocols. As part of monitoring of the intervention on a daily basis, mother’s diary (to record counseling sessions and content of counseling) and CHWs’ reporting tools will be used. The CHWs will be expected to submit weekly reports of their activities to the field coordinator. Close supervision of the activities of the CHWs will be done through regular spot checks and sit-in sessions by the field coordinator.

## Assessment

### Primary outcome

The primary outcome measure is the proportion of children being exclusively breastfed for the first 6 months.

This will involve determining the effectiveness of the BFCI intervention on the level or proportion of children being exclusively breastfed for the first 6 months. The advice and support received by mothers through the intervention is expected to lead to self-efficacy with regards to breastfeeding and effective breastfeeding, hence adherence to WHO guidelines on breastfeeding, resulting in improved levels of exclusive breastfeeding for 6 months. Data on breastfeeding practices will be collected longitudinally from birth every 2 months through an interviewer-administered questionnaire to the mother (24-hour recall at 2, 4, 6 months) with probes on the age at introduction of foods or liquids (if appropriate). Analyses will focus on the differences between the two study arms in the proportion of infants being exclusively breastfed at 6 months, as well as at the two earlier times of 2 and 4 months postpartum.

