### Data collection and analysis

The study will include both qualitative and quantitative standard data collection procedures. Table 4.

**Table 4 Tab4:** Data collection outline

Formative study		
Study objective	Data/variables	Method
1. To establish local contexts and norms, which influence Maternal, Infant and Young Child Nutrition (MIYCN) practices in order to tailor the intervention package to the local communities	Attitudes and practices regarding breastfeeding and other MIYCN practices; cultural and social factors and norms that influence MIYCN	Focus group discussions (FGDs) with community members (women and men and community health workers); key informant interviews (KIIs) with key informants including community administrators and other leaders (e.g. religious group leaders), traditional birth attendants (TBAs); KIIs with facility health workers, CHWs and Sub-County Health Management (ScHMT) team
2. To identify enabling factors and barriers that may influence the implementation of BFCI and potential ways of addressing them	Key players and structures in the community that would facilitate implementation of BFCI (key influential people in the community, community resource persons that would be involved in the implementation of the project, other useful community resources); factors (e.g. socioeconomic, maternal age, social/family support) that influence uptake of interventions in the community; any potential hindrances to the success of the intervention (e.g. myths, beliefs)	Key informant interviews (KIIs) with key informants including community administrators and other leaders (e.g. religious group leaders), traditional birth attendants (TBAs); KIIs with facility health workers, CHWs and (ScHMT) team, FGDs with mothers and fathers
Cluster randomized trial		
Study objective	Variable/Data	Methods
Primary objective		
1. To determine the effectiveness of the BFCI on the rates of exclusive breastfeeding for the first 6 months	Duration of exclusive breastfeeding as a *derived variable*: age of child, current status of breastfeeding (exclusive, mixed feeding, not breastfeeding) with probes on the age at introduction of other foods or liquids (if appropriate), and a 24-hour recall feeding question	Quantitative: questionnaires to mothers and 24-hour recall at 2, 4 and 6 months;
Secondary objectives		

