### Statistical analysis

Analyses will involve comparison of outcomes between the intervention group and the control group using multilevel linear logistic regression and multinomial logistic models that account for clustering.

Determination of differences between the 2 trial arms in the primary outcome (exclusive breastfeeding) will be done at month 2, month 4 and at month 6. Comparison for other outcomes such as morbidity from diarrhea and malnutrition will also be done at months 2, 4 and 6. Analyses will involve a comparison of differences in the intervention and control groups with regard to the primary outcome (exclusive breastfeeding) and secondary outcomes (other infant feeding practices, diarrhea morbidity and nutritional outcomes), controlling for baseline measures (for example, previous breastfeeding practices) and prognostic factors (for example, SES and household food security) if randomization of the clusters does not control for differences in these factors at baseline, through analysis of covariance (ANCOVA). Statistical methods to determine change will include multilevel linear regression for continuous variables (for example, z-scores, multinomial logistic regression analysis for categorical variables: for example, whether exclusively breastfed at 6 months, 4 months or 2 months [32]. Intention-to-treat analysis [33] will be applied as appropriate. Statistical analysis will mostly be done using Stata (StataCorp, College Station, TX, USA). (See Table 5 for detailed outline of data analysis plan).

**Table 5 Tab5:** Data analysis outline

Formative study				
Study objective	Primary outcome variables	Independent variable	Control variables	Type of analysis
1. To establish local contexts and norms, which contribute to maternal infant and young child nutrition (MIYCN) practices so as to customize the intervention package	Factors that influence breastfeeding and other MIYCN practices	Not applicable	Not applicable	Thematic
2. To identify facilitating factors and barriers that may influence the implementation of BFCI	Facilitating factors and barriers to the implementation of BFCI	Not applicable	Not applicable	Thematic
Cluster randomized trial				
Study objective	Outcome variables	Independent variable	Control variables	Type of analysis

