1. To determine the effectiveness of the BFCI on the rates of exclusive breastfeeding for the first 6 months	Exclusive breastfeeding (EBF) at 6 months, 4 months and 2 months	Intervention status	SES, food security, water and sanitation, maternal characteristics, antenatal care	Multinomial logistic regression
2. To determine the effectiveness of BFCI strategy on MIYCN knowledge and attitudes	a. Knowledge levels on MIYCN	Intervention status	SES, food security, water and sanitation, maternal characteristics, antenatal care	Logistic regression
	b. Attitudes on MIYCN			
3. To determine the effectiveness of the BFCI on rate of initiation of breastfeeding within the first hour of birth and its implications on successful EBF for the first 6 months	Initiation of breastfeeding within 1 hour	Intervention status	SES, food security, water and sanitation, maternal characteristics, antenatal care	Logistic regression
4. To assess the change in nutritional and health status among infants and young children from the implementation of BFCI	a. Stunting	Intervention status	SES, food security, water and sanitation maternal characteristics, antenatal care, vaccination status	Logistic regression for stunting, underweight and wasting
	b. Underweight			ANCOVA for *z*-scores and multilevel modeling for diarrhea morbidity
	c. Wasting			
	d. *z*-scores			
	e. Diarrheal and other morbidity			
5. To determine the factors and barriers associated with the implementation of BCFI and how to address them	a. Satisfaction with intervention	Not applicable	Not applicable	Descriptive (Outcome 1)
	b. Experiences with intervention			Qualitative: Thematic analysis (Outcomes 2 and 3)
	c. Limiting and enabling factors			

*ANCOVA* analysis of covariance, *BFCI* Baby Friendly Community Initiative, *SES* socio-economic status

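### The primary outcome is exclusive breastfeeding for the whole first 6 months, but the analysis sections compare feeding status at months 6, 4 and 2 and never use the derived duration

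*Protocol article*

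**What the plan says.** **Whole-period version.** Under Primary outcome, the Protocol article states: "The primary outcome measure is the proportion of children being exclusively breastfed for the first 6 months". The first listed aim in Background, the planning rates under Sample size considerations (32% and 50%) and the wording of objective 1 in Tables 4 and 5 all refer to the same period.

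**Point-status version.** The same Primary outcome section then says that the analyses will focus on "the proportion of infants being exclusively breastfed at 6 months, as well as at the two earlier times of 2 and 4 months postpartum". Statistical analysis gives the categorical variable as "whether exclusively breastfed at 6 months, 4 months or 2 months". The outcome column of Table 5, objective 1, reads "Exclusive breastfeeding (EBF) at 6 months, 4 months and 2 months".

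**Data collected.** Primary outcome describes a questionnaire with "24-hour recall at 2, 4, 6 months) with probes on the age at introduction of foods or liquids". Table 4 lists, for the primary objective, "Duration of exclusive breastfeeding as a *derived variable", built from the child's age, current feeding status, the probes and the recall.

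**Counselling.** On the content of counselling, Intervention says: "It will also focus on age-appropriate complementary feeding, starting at 6 months". Background adds that follow-up stops at 6 months, the age at which other foods are expected to begin.

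**The concern.** Exclusive breastfeeding for 6 months is a statement about a history. Exclusive breastfeeding at 6 months, read from a 24-hour recall, is a statement about one day. The two can disagree in both directions:

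- An infant given water at 1 month, but only breast milk on the day before the 6-month interview, fails the stated outcome and passes the point-status one.
- An infant exclusively breastfed for 6 months and then started on food, interviewed shortly afterwards, passes the stated outcome and fails the point-status one.

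The second case matters here because the last assessment falls at the age when the trial's own counselling tells mothers to begin other foods. If that counselling makes timely introduction more common in the intervention arm, more of that arm's true successes could be scored as failures.

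At stake is whether the reported effect answers the stated primary question. Either error shrinks the difference between arms in the illustrations below, so a real effect could be underestimated or missed. In addition, Statistical analysis applies the term primary outcome to the comparisons at months 2, 4 and 6 together, which blurs which one carries the claim.

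**Working it through.** **1. Side by side.** In Table 5, objective 1, the objective column refers to the first 6 months as a period and the outcome column to status at three ages. The same pair occurs within Primary outcome. Table 4's derived duration would join them, but neither Statistical analysis nor Table 5 mentions it. No rule says how the probes alter the scoring at 6 months, and no window is given for the 6-month visit.

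**2. The plan's sample size.** Inputs from Sample size considerations: 32% v 50%, two-sided 5%, power 80%, intracluster correlation 0.035, average cluster size 62.5, loss 10%.

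- Per arm before clustering, pooled-variance formula, mean rate 0.41: n = [1.96·√(2·0.41·0.59) + 0.8416·√(0.32·0.68 + 0.50·0.50)]² / 0.18² = 116.01, rounded up to 117.
- Design effect: 1 + (62.5 − 1)·0.035 = 3.1525, stated as 3.15.
- 117·3.15 = 368.55, rounded up to 369 per arm, or 738 in total.
- 738·1.10 = 811.8, rounded up to 812.

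Both stated figures reproduce. The inputs are described as exclusive breastfeeding for 6 months, so the calculation matches the stated outcome, not the point-status analysis.

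**3. Illustration of size.** The documents give no misclassification rate; every f and g below is an assumption. The effective size per arm is m = 369/3.15 = 117.1. With d = p1 − p0 and p̄ the mean of the two rates:

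power = Φ{ [d·√m − 1.96·√(2p̄(1 − p̄))] / √(p0(1 − p0) + p1(1 − p1)) }

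Undistorted (32% v 50%), this gives 80.4%.

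*A fraction f of adherent infants scored as failures in both arms; each rate is multiplied by (1 − f):*

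| f | control | intervention | difference | power |
|---|---|---|---|---|
| 5% | 30.4% | 47.5% | 17.1 points | 76.9% |
| 10% | 28.8% | 45.0% | 16.2 points | 73.2% |
| 20% | 25.6% | 40.0% | 14.4 points | 65.2% |

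*The same error in the intervention arm only; control stays at 32%:*

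| f | intervention | difference | power |
|---|---|---|---|
| 5% | 47.5% | 15.5 points | 68.1% |
| 10% | 45.0% | 13.0 points | 53.4% |
| 20% | 40.0% | 8.0 points | 24.6% |

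With the unpooled standard error √[DE·(p0q0 + p1q1)/369] and the planned 61.5 infants per cluster (738/12; DE = 1 + 60.5·0.035 = 3.12), the 10% row gives about 54.5%. Hence the range 53–55%.

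*Opposite error: a fraction g of infants with earlier lapses scored as exclusive in both arms; each rate p becomes p + g(1 − p):*

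- g = 10%: 38.8% v 55.0%, difference 16.2 points, power 70.2%.
- g = 20%: 45.6% v 60.0%, difference 14.4 points, power 59.9%.

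**4. When would the sign reverse?** With no misscoring in control, 0.50·(1 − f) < 0.32 requires f > 1 − 0.32/0.50 = 36%, confined to the intervention arm.

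**The case against.** The strongest defence is that no sentence says the outcome will be scored from the recall alone. The recall is paired with "with probes on the age at introduction of other foods or liquids (if appropriate), and a 24-hour recall feeding question", and Table 5 is a condensed outline under an objective worded as the whole period. Status at 6 months could therefore mean exclusive up to that age. This is a possible reading, and it rules out saying that recall-only scoring is certain. It does not settle the matter, because the analysis sections never refer to the derived duration, while Discussion relies on the 24-hour recall and repeated questioning as the safeguard for this outcome.

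The visit-timing mechanism is also unproven. Data are collected until the child is 6 months old, and a recall taken on the day the child reaches that age covers the preceding day. Nothing in the article schedules later visits. This stands: the possibility is real, but its frequency is unknown.

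Four stronger inferences are tempting and not supported:

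- **The effect could be reversed.** That needs more than 36% misscoring in the intervention arm and none in control; nothing in the article suggests it.
- **The error is differential by design.** Control mothers also receive educational materials on maternal, infant and young child nutrition, and general nutrition counselling. Intervention counselling is more intensive, so a difference between arms is possible, but its size is unknown.
- **The three months have no order, so the type I error is inflated.** Primary outcome names one measure and puts 6 months first, and the sample size is for 6 months only. The looser wording in Statistical analysis needs tidying, but nowhere is success at any one month declared sufficient.
- **The 32% planning rate uses the wrong definition.** Study setting and Sample size considerations both label it as exclusive breastfeeding for 6 months, and its source is not available here.

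**Conclusion.** The point holds as an internal inconsistency: followed as written, the variable compared is not the outcome defined, and the derived variable that would reconcile them is left out of the analysis. It is read at the age when the intervention counsels other foods, so some adherent mothers can be counted as failures, possibly more in the intervention arm.

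The size cannot be fixed from the article. The losses from about 80% power to about 73% (10% in both arms) or 53–55% (10% in the intervention arm only) are illustrations; they rest on assumed misscoring rates, the plan's 32% and 50%, its design effect and 369 evaluable infants per arm. If all 6-month recalls refer to a day before 6 completed months, the second error largely disappears; missed earlier lapses remain unless the probes are used. The sample size needs no change on this account.

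**What to change.** 1. Define one primary endpoint: no food or liquid other than breast milk introduced before 6 completed months. Derive it from the age-at-introduction probes and the recalls at all visits, and count any non-exclusive recall before 6 months as a failure.
2. Have the 6-month recall refer to a day before 6 completed months.
3. Label status at months 2 and 4 as secondary.
4. Align Primary outcome, Table 4, Statistical analysis and Table 5 with this definition.

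The cost is revised endpoint wording and an instruction on the 6-month recall. No new data items are needed, and 738/812 stands. The downside is that reported rates may be lower than point prevalence.
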